## Abstract

**Background:**

Radiotherapy delivery regimens can vary between a single fraction (SF) and multiple fractions (MF) given daily for up to several weeks depending on the location of the cancer or metastases. With limited evidence comparing fractionation regimens for oligometastases, there is support to explore toxicity levels to nearby organs at risk as a primary outcome while using SF and MF stereotactic ablative radiotherapy (SABR) as well as explore differences in patient-reported quality of life and experience.

**Methods:**

This study will randomize 598 patients in a 1:1 ratio between the standard arm (MF SABR) and the experimental arm (SF SABR). This trial is designed as two randomized controlled trials within one patient population for resource efficiency. The primary objective of the first randomization is to determine if SF SABR is non-inferior to MF SABR, with respect to healthcare provider (HCP)-reported grade 3-5 adverse events (AEs) that are related to SABR. Primary endpoint is toxicity while secondary endpoints include lesional control rate (LCR), and progression-free survival (PFS). The second randomization (BC Cancer sites only) will allocate participants to either complete quality of life (QoL) questionnaires only; or QoL questionnaires and a symptom-specific survey with symptom-guided HCP intervention. The primary objective of the second randomization is to determine if radiation-related symptom questionnaire-guided HCP intervention results in improved reported QoL as measured by the EuroQoL-5-dimensions-5levels (EQ-5D-5L) instrument. The primary endpoint is patient-reported QoL and secondary endpoints include: persistence/resolution of symptom reporting, QoL, intervention cost effectiveness, resource utilization, and overall survival.

**Discussion:**

This study will compare SF and MF SABR in the treatment of oligometastases and oligoprogression to determine if there is non-inferior toxicity for SF SABR in selected participants with 1-5 oligometastatic lesions. This study will also compare patient-reported QoL between participants who receive radiation-related symptom-guided HCP intervention and those who complete questionnaires alone.

**Trial registration:**

Clinicaltrials.gov identifier: NCT05784428. Date of Registration: 23 March 2023.

**Supplementary Information:**

The online version contains supplementary material available at 10.1186/s12885-024-11905-7.

## Background

The oligometastatic state refers to a stage of disease where a cancer has spread beyond the site of the primary tumour, but is not yet widely metastatic [1]. In patients with a limited oligometastatic burden, emerging evidence suggests that treatment of all sites of disease with ablative therapies such as surgery or stereotactic ablative radiotherapy (SABR) can improve patient outcomes, including overall survival (OS) and progression-free survival (PFS) [2, 3]. The oligoprogressive state is similar to the oligometastatic state; however, there are some key distinctions. Oligoprogression is the progression of limited metastases following an initial response to systemic treatment [2]. In contrast to the oligometastatic state, the oligoprogressive state can have any number of metastases as long as these were, at one point, controlled [3]. The oligoprogressive state is being seen more often in clinical encounters [2], potentially due to increased utilization of targeted therapies and subsequent acquired resistance of a subpopulation of tumour cells [2, 4]. Recent research has shown that stereotactic ablative strategies might be appropriate for the treatment of the oligoprogressive state although less evidence exists than for the oligometastatic state [5].

Historically, treatment for patients with both oligometastatic and oligoprogressive cancers have been predominantly based on systemic therapies (chemotherapy, hormonal, targeted and immunotherapies) with the intent to delay progression and extend life. However, emerging evidence, suggests that treatment of all oligometastatic sites with ablative therapies such as surgery or SABR are associated with favorable outcomes [6–8]. SABR is a modern technique that delivers high doses of radiotherapy (RT) to tumour targets using highly conformal techniques. Modern SABR techniques effectively limit dose to nearby organs while escalating the tumour dose and achieving excellent rates of local control. However, as there is a potential for higher toxicity, SABR requires extensive planning and time on the treatment unit to deliver each fraction safely, compared to conventional RT, thus resulting in higher costs. Based upon existing randomized evidence supporting SABR for oligometastatic cancer and emerging evidence for benefit also in the oligoprogressive state, we should explore optimizing SABR treatment regimens in order to maintain favorable toxicity profiles and oncologic outcomes while potentially improving cost-efficacy and patient convenience.

RT delivery regimens can vary between a single fraction (SF) and multiple fractions (MF) given daily for up to several weeks depending on the location of metastases, while SABR is generally limited to eight or fewer fractions. MF RT is administered to reduce the radiation load given at a single event, which may reduce late toxicities. However, SF RT may be more cost effective and reduces patient treatment time. While SF SABR is a safe and effective treatment for brain metastases, the toxicity profile for other metastatic sites and in the setting of oligometastases is not well established. One study comparing SF with MF SABR in treatment of 1-3 pulmonary oligometastases showed no statistically significant difference in toxicities or OS between the groups, however, this was a retrospective study and limited to a small sample size [9]. The recent randomized phase 2 SAFRON II trial reported no difference between SF and MF SABR for lung oligometastases in the primary endpoint of severe toxicity, and also similar local control, survival and qualify-of-life (QoL) between treatment arms [10, 11]. Another recently completed phase III randomized controlled trial (RCT) comparing local control of oligometastases between SF and MF SABR found significantly lower cumulative incidence of local recurrence in the SF arm [12]. However, the biologically equivalent dose for the MF arm was significantly lower than for the SF arm, thereby limiting the study’s interpretation and generalizability. We have found no studies that have investigated SF vs. MF for oligoprogression. Consensus among radiation oncologists and our patient partners was to perform a study with toxicity as the primary outcome given concerns that SF SABR may have a higher rate of toxicity to nearby organs at risk. It is critical that a properly powered phase III trial is conducted comparing toxicity, efficacy, and cost-effectiveness between SF and MF SABR with similar biologically effective doses, a larger sample size, and inclusive of all tumour sites to expand our knowledge of SABR in both oligometastatic and oligoprogressive settings and to guide evidence-based prescription of SF SABR.

In a study by Basch et al., changes in QoL in patients receiving outpatient chemotherapy for advanced solid tumours were compared [13]. Patients were randomly assigned to complete symptom monitoring electronically, or received standard of care, and results in this systemic therapy population showed a greater improvement in QoL and OS from baseline to 6 months in the symptom monitoring arm. Our study will implement similar methodology in the radiotherapy setting. We will examine differences in patient-reported QoL in the second randomization, comparing change in EQ-5D-5L scores between those who complete questionnaires alone and those who complete questionnaires, a symptom-specific survey and receive HCP-guided intervention.

## Methods

The objective of this trial is to assess if there is non-inferiority in terms of HCP-reported grade 3 or higher toxicities, lesional control rate (LCR), PFS, cost-effectiveness, and OS in patients with 1-5 oligometastatic or oligoprogressive lesions receiving SF SABR compared to patients receiving MF SABR. The trial will also assess if radiation-related symptom questionnaire-guided HCP intervention provides improvement in patient-reported QoL, compared to no HCP intervention in a subset of sites. The methods to be employed in this trial follow similar methodology used in our current SABR-COMET-3 trial [14].

### 1st randomization

#### Primary endpoint

##### Toxicity

◦ Defined as grade 3-5 adverse events (Common Terminology Criteria for Adverse Events [CTCAE] version 5.0) that are possibly, probably, or definitely related to SABR.

#### Secondary endpoints

##### LCR

◦ Assessed using the Tumour Lesion Measurement form. Rate is determined based on lesion size post-SABR using Response Evaluation Criteria in Solid Tumours (RECIST) version 1.1.

##### OS (exploratory)

◦ Time from randomization to death from any cause, or last follow-up, whichever occurs first.

##### PFS

◦ Time from randomization to disease progression at any site, death, or last follow-up, whichever occurs first.

##### QoL

◦ Assessed via Functional Assessment of Cancer Therapy: General (FACT-G)

##### QoL

◦ Assessed via EQ-5D-5L questionnaire.

##### Resource utilization

◦ Assessed via Patient- and Provider-Reported number of hospital admissions, emergency room (ER) visits, systemic or RT.

### 2nd Randomization (BC Cancer sites only)

#### Primary endpoint

##### Differences in patient reported QoL

As measured by the EQ-5D-5L based on presence or absence of HCP intervention (guided by symptoms reported in the generic radiation-related symptom questionnaire).

#### Secondary endpoints

##### Patient hospitalization and emergency department visit rates

◦ Captured in self-reported forms and as reported by the HCP.

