##### Cost-effectiveness of Patient Reported Outcome (PRO)-guided intervention

◦ Assessed via Patient- and Provider-Reported resource utilization forms

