### Standard arm – QoL questionnaires only (ARM A)

0-3 days prior to each scheduled patient visit on trial, patients will be prompted to complete the EQ-5D-5L and FACT-G questionnaires [16, 17]. Questionnaire data will be saved in the study database.

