### Experimental arm – QoL questionnaires and symptom-specific intervention (ARM B)

0-3 days prior to each scheduled study visit on trial, patients will be automatically prompted to complete the EQ-5D-5L, FACT-G as well as a PRO symptom screen utilizing a generic radiation-related symptom questionnaire. In addition, patients may report symptoms *ad hoc,* with a response by the HCP within three working days. Depending on symptoms entered, patients may receive HCP-guided intervention such as symptom management advice or referral to family physician.

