### QA for 2^nd^ randomization

Clinical trial staff will provide a 5-20 minute training session to participants randomized to Arm B on how to use a patient outcomes management tool for self-reporting of symptoms at time of enrollment. Electronic entry platform will be configured to send an email alert to a HCP when a patient-reported symptom meets notification criteria.

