### Cost Utility Analysis (CUA)

A CUA will be conducted in line with the Canadian Agency for Drugs and Technologies in Health (CADTH) Guidelines for the Economic Evaluation of Health Technologies [24, 25]. Non-parametric bootstrapping will be used to estimate the 95% confidence intervals (CIs) and to construct a cost-effectiveness acceptability curve. Sensitivity analysis will be conducted by varying the major drivers of costs. All costs will be adjusted to a base year using the healthcare component of the Statistics Canada Consumer Price Index [26] to adjust for price inflation over time. Subsequent incremental cost per unit of OS improvement using OS outcomes will be explored. Although Canada has a single-payer health insurance system, the provincial and territorial governments are responsible for health care administration and delivery. Our analyses will be undertaken from the perspectives of the British Columbia and Ontario provincial Ministries of Health as we expect these provinces to accrue the highest number of patients. We will gain consent from all trial participants to prospectively assess their patient-level records pertaining to the frequency of hospital admissions and the use of targeted- and immuno-therapies. We will use the resource costing method whereby utilization data are collected from existing data sources and then multiplied by unit costs.

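### Admissions and emergency visits in Arm A versus Arm B rest partly on HCP report, and only Arm B has extra HCP contact, so events may be recorded more completely there

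*Protocol article*

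**What the plan says.** All places are in the protocol article.

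- **Endpoint.** Under 2nd Randomization, Secondary endpoints, hospitalization and ED visit rates are "Captured in self-reported forms and as reported by the HCP". No other source is named for this endpoint.
- **Cost-effectiveness of the PRO-guided intervention.** This is "Assessed via Patient- and Provider-Reported resource utilization forms", so it draws on the same two informants.
- **Arm A.** Patients complete EQ-5D-5L and FACT-G before scheduled visits. "Questionnaire data will be saved in the study database", and no HCP action is attached.
- **Arm B.** A symptom screen is added before scheduled visits. In addition, "patients may report symptoms *ad hoc,* with a response by the HCP within three working days". The section QA for 2nd randomization says the electronic platform will be "configured to send an email alert to a HCP when a patient-reported symptom meets notification criteria".
- **Blinding.** Study design describes the trial as open-label.
- **Another source for admissions.** Cost Utility Analysis (CUA) plans to obtain consent from all participants to "prospectively assess their patient-level records pertaining to the frequency of hospital admissions" and to take utilization from existing data sources. It does not name ED visits, and it is not linked to the two endpoints above.

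**The concern.** The randomized difference between Arms A and B is, in large part, extra contact with an HCP. HCP report is also one of the two sources for this endpoint, so one measurement channel can depend on the arm. The symptoms that prompt an alert or an ad hoc report are the kind that may accompany an ED visit or admission, and an HCP who responds to them can learn of an event that would otherwise go unreported. Arm A has no matching channel, and blinding gives no protection.

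Any such effect adds recorded events in Arm B. A real reduction in admissions or ED visits would be diluted. A null effect could look like an excess, and the resource use charged to the intervention would be inflated. Analysis cannot readily repair differential collection afterwards, so the source is best fixed in the protocol.

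A true effect of the extra contact on admissions or ED visits is a different matter. It belongs to the intervention and should stay in the comparison.

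**Working it through.** The article states no event rate, effect size or power for this endpoint, so there is no figure to reproduce. The check has two parts.

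**1. Does the source depend on the arm?**

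| Source | Arm A | Arm B | Can it depend on the arm? |
|---|---|---|---|
| Patient report | yes | yes | No separate resource-use form is described for either arm |
| HCP report | yes | yes, plus alerts and ad hoc contact | Yes |
| Patient-level admission records (CUA section) | all participants | all participants | No, but not linked to this endpoint and silent on ED visits |

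**2. How large could the effect be?** Every input here is assumed; none is in the document. Let *s* be the share of events that patients report themselves, and *h* the share of the remaining events that the HCP picks up. Assume that an event is counted if either source reports it. Then

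capture = *s* + (1 − *s*)*h*, and observed ratio B/A = true ratio × capture in B ÷ capture in A.

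| *s* | *h* in A | *h* in B | Capture A | Capture B | Ratio if no true effect | A true 0.80 appears as |
|---|---|---|---|---|---|---|
| 0.80 | 0.50 | 0.50 | 0.90 | 0.90 | 1.00 | 0.80 |
| 0.80 | 0.50 | 0.60 | 0.90 | 0.92 | 1.02 | 0.82 |
| 0.90 | 0.25 | 0.75 | 0.925 | 0.975 | 1.05 | 0.84 |
| 0.80 | 0.25 | 0.75 | 0.85 | 0.95 | 1.12 | 0.89 |
| 0.70 | 0.25 | 0.75 | 0.775 | 0.925 | 1.19 | 0.95 |

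Example, fourth row: A = 0.80 + 0.20 × 0.25 = 0.85; B = 0.80 + 0.20 × 0.75 = 0.95; 0.95 ÷ 0.85 = 1.12; 0.80 × 1.12 = 0.89.

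**Effect on a test.** Take 125 patients per arm (the number in Sample size calculation, 2nd randomization, set there for QoL), a two-sided 5% unpooled z test, and the proportion of patients with an event. With no true difference, capture of 85% versus 95% and a true proportion of 30%, the observed proportions are 0.255 and 0.285. The standard error is √(0.255 × 0.745/125 + 0.285 × 0.715/125) = 0.056, so the shift is 0.030 ÷ 0.056 = 0.53 standard errors. The rejection probability is then 8.3% instead of 5%. For true proportions of 20% and 40% it is 7.0% and 10.1%. With 90% versus 95% capture it is 5.5% to 6.2% over the same range of true proportions.

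**The case against.** The strongest reply is that the Arm B channel carries symptoms. No section says that admissions or ED visits are logged through it. Resource use has its own forms, and the first randomization also relies on patient and provider reports of admissions and ER visits, so this looks like trial-wide capture. No section gives the two arms different resource-use forms or visit schedules. Only the optional ad hoc reports are explicitly outside the visit schedule; the symptom screen is tied to scheduled visits. **This stands.** It is why the point is that recording may differ. A reader might infer that the same event is more likely to be recorded in Arm B, but the document does not establish that.

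A reader might also infer that an event counts whenever either informant reports it. The article joins the two sources with a plain conjunction and gives no combination rule. That rule may sit in the full protocol or analysis plan, and its absence from an article is no fault. The either-source rule above is a working assumption. Nor does the article call this a harm endpoint.

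The size depends wholly on the assumed gap in HCP pick-up. Equal pick-up gives 1.00, and 50% versus 60% gives 1.02. **This also stands:** the table shows sensitivity and does not estimate the bias.

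For admissions, the CUA section already plans an arm-independent source. That narrows the problem but does not close it, because the two second-randomization endpoints name only patient and provider reports. ED visits have no such source.

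Finally, the endpoint is secondary, has no stated power, and does not drive the interim decision on Arms A and B, which rests on QoL. That limits the weight of the point.

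**Conclusion.** The concern holds as a risk of differential ascertainment built into the stated sources, mainly for ED visits, and for admissions as long as the planned records are not used for this endpoint. Its likely direction is against the symptom-guided intervention. Its size cannot be derived from the document: the ratio under no true effect is 1.00 with equal HCP pick-up and about 1.02 to 1.19 under the assumed gaps, so that a true 0.80 would show as about 0.82 to 0.95. These figures rest on assumed self-report of 70% to 90%, assumed HCP pick-up by arm, and an either-source counting rule.

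The document does not show that bias will occur, and neither primary endpoint is affected. This is a cheap improvement to a secondary comparison and to the cost-effectiveness result that shares its sources.

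**What to change.** **Admissions.** In the second-randomization entries for hospitalization and ED visit rates and for cost-effectiveness, state that admissions for A versus B come, in both arms, from the patient-level records already planned under Cost Utility Analysis. Confirm that these records will cover both arms over the same follow-up.

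**ED visits.** Base the primary comparison on the same resource-utilization forms, completed at the same scheduled visits in both arms. Report visits known only through an Arm B alert or ad hoc contact separately, and add a sensitivity analysis that includes them.

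Counting ED visits from patient self-report alone is tempting but goes too far. In the 80% self-report example it would cut capture from 85% to 80% in Arm A and from 95% to 80% in Arm B, discarding HCP-reported visits that identical scheduled forms can keep.

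**Cost.** This is mainly a wording change, because access to admission records is already foreseen. Some ED visits known only through unscheduled contact leave the primary count, mostly in Arm B. The remedy is also not perfect: an HCP completing a scheduled form in Arm B may already know of an event from earlier contact, and only Arm B patients are trained in symptom self-reporting. The separate listing and the sensitivity analysis show how much depends on the unscheduled contacts.

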##### Cost-effectiveness of Patient Reported Outcome (PRO)-guided intervention

◦ Assessed via Patient- and Provider-Reported resource utilization forms

##### OS (exploratory)

◦ Time from randomization to death from any cause, or last follow-up, whichever occurs first.

## Study design

This is a phase III, investigator-led, open-label, multi-institutional, RCT using a 2x2 factorial design with two randomizations and two primary outcomes. Participating institutions will be tertiary, academic hospitals or RT treatment institutions in Canada, the United Kingdom, United States, and Australia (updated country list available on ClinicalTrials.gov entry NCT05784428). The first and primary randomization is by dose and fractionation, while the second randomization is by HCP-led intervention based on PRO symptom screen, as displayed in schema Fig. 1.

**Fig. 1 Fig1:**
[figure not shown]
Study schema

## Inclusion criteria

◦ Total number of current metastases of 1-5 (either oligometastatic or oligoprogressive lesions)◦ Age 18 years or older◦ Able to provide informed consent◦ Able to complete electronic entry (mandatory for BC Cancer sites) or paper entry of patient-reported outcomes independently or with assistance from a caregiver/family/friend/research staff using electronic methods after providing consent for use of email◦ Eastern Cooperative Oncology Group (ECOG) performance status 0 – 2◦ Life expectancy > 6 months◦ Histologically confirmed malignancy with metastatic disease detected on imagingBiopsy of metastasis is preferred, but not required◦ Controlled primary tumourdefined as: at least 3 months since original tumour treated definitively, with no progression at primary site (can be considered controlled if no evidence of primary tumour on imaging [e.g. primary unknown])◦ A history and physical examination including ECOG performance status performed within 6 weeks prior to trial enrollment◦ Patient has had a computed tomography (CT) chest, abdomen and pelvis or positron emission tomography (PET-CT) within 8 weeks prior to enrollment, and within 12 weeks prior to treatment. CT neck as clinically indicated◦ Patient has had a nuclear bone scan (if no PET-CT) within 8 weeks prior to enrollment, and within 12 weeks prior to treatment◦ If solitary lung nodule for which biopsy is unsuccessful or not possible, patient has had an fluorodeoxyglucose (FDG) PET scan or CT (chest, abdomen, pelvis) and bone scan within 8 weeks prior to enrollment, and within 12 weeks prior to treatment. CT Neck as clinically indicated◦ If colorectal primary with rising carcinoembryonic antigen (CEA), but equivocal imaging, patient has had an FDG PET scan within 8 weeks prior to enrollment, and within 12 weeks prior to treatment◦ Patient has had CT or magnetic resonance imaging (MRI) of brain if primary has a propensity for central nervous system (CNS) metastasis within 8 weeks prior to enrollment, and within 12 weeks prior to treatment◦ For patients with known spine metastases, patient has had MRI spine imaging within 8 weeks prior to enrollment, and within 12 weeks prior to treatment.◦ Patient is judged able to:Maintain a stable position during therapy.Tolerate immobilization device(s) that may be required to deliver SABR safely◦ Negative pregnancy test for People of Child-Bearing Potential (POCBP) ***within 4 weeks of RT start date***

